### Physical activity stimulation program

The physical activity stimulation program consists of a 6-month tailored lifestyle intervention and a 4-month fitness training program. The fitness training will replace the regular pediatric physiotherapy aimed at improving fitness or functional mobility. After the fitness training program, regular pediatric physiotherapy will be resumed during the last two months of the lifestyle intervention (see Figure 1). When there is a need for additional physiotherapy, aimed at maintaining range of motion or muscle length, this will be continued during the fitness training program.

#### Lifestyle intervention

The purpose of the lifestyle intervention is to maintain or increase physical activity and to initiate a shift towards a more active lifestyle. To that end, a 6-month lifestyle intervention has been developed, consisting of: 1) counseling children and parents to adopt an active lifestyle through Motivational Interviewing[27], and 2) home-based physiotherapy to practise mobility-related activities in the daily situation. At the start of the intervention the child and the parents together will be visited at home for a first counseling session, during which they will also be interviewed about their attitudes towards sports, physical activity of the child, and any problems they experience that are related to daily life mobility or sports. The child and the parents will be asked to rate these problems on a 10-point scale, resulting in a problem score. Based on the interview and the possible problem score, the content of the following counseling sessions and the home-based physiotherapy will be individually tailored.

Counseling is aimed at motivating the child and the parents to adopt a more active lifestyle. It consists of one or two home visits, parents visiting the fitness training, a sports workshop for the children, and one or two follow-up telephone calls. During the home visit and follow-up telephone calls the child and the parents will receive counseling, based on the Motivational Interviewing technique[27]. This is a directive and client-centered interview style that is intended to bring about behavioral change, like achieving a more active lifestyle. During the counseling, the interviewer will introduce some basic lifestyle themes (such as satisfaction with present lifestyle, and attitude towards a more active lifestyle), and will try to elicit statements concerning desire, ability, and reasons and need for changing the present lifestyle[27]. During this process the interviewer will not challenge resistance to change, but will go along with the resistance and will explore the ambivalence of the child or the parents with regard to a change in lifestyle. The interviewer then will structure possible ambivalence, in order to help the child and the parents to prioritize arguments for changing ('change talk') or not changing. When there is sufficient motivation for change, the interviewer will change the focus of the counseling to reinforce 'change talk' and to help the child and the parent to set specific goals for achieving an active lifestyle.

Home-based physiotherapy is aimed at increasing the capacity of daily activities in the home situation, in the playground or at school. The child will receive training in certain daily activities, based on the mobility problems indicated by the child and/or the parents (such as getting into the car, going up stairs carrying something, and skating). The physiotherapist will make a maximum of four visits, starting when the frequency of the fitness training has decreased to once a week (see Figure 1).

Whether or not the lifestyle intervention has been successful, will be evaluated only in the intervention group by means of the problem score and the stages of change according to Prochaska et al.[28].

#### Fitness training program

The fitness training program is aimed at increasing muscle strength and cardiovascular fitness. To increase muscle strength, the focus will be on the lower extremity extensor muscles, because the lower extremities are mainly used to perform mobility-related activities in ambulatory children with CP. It has recently been reported that children with CP can improve the strength of their lower extremity extensor muscles by means of a 12-week functional progressive resistance exercise program[29]. Cardiovascular fitness can be improved in children, by training both aerobic and anaerobic capacity. Recently, Verschuren et al.[30] reported a relationship between gross motor functioning and cardiovascular fitness in children with CP. They found a moderate to strong relationship between gross motor functioning and anaerobic capacity, but no relationship between gross motor functioning and aerobic capacity. Therefore, training anaerobic capacity seems to be most relevant for our study population. Moreover, in a recently published paper it was reported that children with CP can improve their anaerobic capacity by means of a 4-month anaerobic training program[14]. The results of that study also indicated that anaerobic training can improve aerobic capacity as well as functional muscle strength. This is in accordance with the results of a study of typically developing children, that showed an increase in aerobic capacity after anaerobic training[31].

To achieve optimal compliance with training, it is important that the children enjoy the training. The fitness training will therefore be performed in groups of two to five children and most of the exercises will be the form of in games. The fitness training will last for four months: twice a week in the first two months, and then once a week in the following two months. The frequency will be reduced to once a week to provide the opportunity to start participating in other physical activities, such as training in a sports club. Each training session will last for one hour, starting with a 5-minute warming-up period. This will be followed by the core part of the training, consisting of two muscle strengthening exercises and three anaerobic exercises. Each training session will end with a cooling down period. Figure 2 presents an overview of a training session. The children wear their usual orthoses or orthopedic shoes during the training sessions. All the physiotherapists will have to attend workshops in which they receive instructions about the fitness training.

**Figure 2 F2:**
[figure not shown]
**A LEARN 2 MOVE 7-12 fitness training session**.

Lower-extremity muscle strength will be trained in a functional way with weight vests, based on the progressive strength training protocol developed by Scholtes et al.[32]. In line with the current guidelines for muscle strength training in children[33], the training load is set at three sets of 12 repetitions at the 12-repetition maximum (12RM), and will be gradually increased from only bodyweight to 100% of the 12RM. Predicted values of the 12RM, based on GMFCS level and bodyweight, are used to determine the initial training load (predicted 12RM for GMFCS I: 26% bodyweight; GMFCS II: 20% bodyweight; GMFCS III: 17% bodyweight) based on previous data[29]. The children will perform two functional strengthening exercises during each training session: 1) a *loaded sit-to-stand*, and 2) a *loaded **game*. These exercises have been chosen because they involve the large muscle groups of the lower extremities which are needed for several functional mobility skills, such as rising from a chair, rising from the ground, climbing stairs, running, and stepping over obstacles.

*The loaded sit-to-stand (STS) *will be performed on a height-adjustable chair, starting with hips and knees in 90 degrees of flexion. The children have to rise from the chair in two-three seconds, and sit down again in two-three seconds, wearing a weight vest in which 'soft lead' can be placed to increase the training load. In the first week of the training the children will perform one to three sets of 12 repetitions of the loaded STS with no load (bodyweight) to get used to the exercise and the weight vest. In the second week of the training they will perform three sets of 12 repetitions with a 60-second rest interval, with a load of 40% of the predicted 12RM. When two sets of 12 repetitions are performed adequately (with fluent speed, without moving the trunk forward rapidly to initiate the movement, and without falling down on the chair seat), the children will be encouraged to perform 15 repetitions in the third set. If adequately performed, the training load will then be increased with 10-20% of the predicted 12RM. This process will be repeated during each training session (see Table 1). Since the loaded STS will be performed with a high load, this exercise is not integrated in a game.

**Table 1 T1:** Progressively building up training load of the loaded sit-to-stand

Week	Goal	Sets	Repetitions	Load	Rest
**1**	Familiarization, focus on adequate performance	1-3	12	Bodyweight	60s

**2**	Familiarization with weight vest, focus on adequate performance	1-3	12	40% pred12RM	60s

**3**	Built up training intensity	1-2 3	12 12-15 (max)^1^	+10-20% pred12RM^1^	60s

**4-16**	Increase Strength	1-2 3	12 12-15 (max)^1^	+10-20% pred12RM^1^	60s

Abbreviation: Pred12RM = predicted 12 repetition maximum.

^1 ^If 15 repetitions are adequately performed, load is increased with 10-20% of the predicted 12RM.

*The loaded game *can vary, depending on the GMFCS level, and consists of: a) the STS, b) the forward step-up, c) the lateral step-up, or d) the half-knee rise. The training load will be set at three sets of 12 repetitions with 25% of the training load used in the loaded STS. In the first week the loaded game will be performed with only bodyweight for three sets of 12 repetitions with a 60-second rest interval. In the first three weeks the load will be increased to 25% of the predicted 12RM, and will be further increased with the loaded STS increase (25% of the load during the loaded STS). Children who are initially unable to accomplish three sets of 12 repetitions adequately, will perform the strengthening exercises with less repetitions per set and/or less sets at bodyweight until three sets of 12 repetitions will be achieved. The load will only be increased when three sets of 12 repetitions are performed adequately. The loaded game can be integrated in a game.

Anaerobic capacity will be trained the form of in games by means of three task-specific exercises (such as running or playing with a ball), that last for 15-20 seconds, each performed at maximal intensity. The training protocol developed by Verschuren et al.[14] serves as a basis for the anaerobic fitness training. To achieve a progressive work-load, the duration of the exercise will be increased and/or the rest periods will be decreased during the training period (see Table 2). In between the exercises, the children will have an active rest period (not sitting down), varying from 60 to 80 seconds, as determined by the work:rest ratio. The work:rest ratio starts at 1:5 in the first week, decreases to 1:4 in the second week, and to 1:3 in the 15^th ^week. The physiotherapists are allowed to vary the exercises or make up new exercises, as long as the children will perform the exercises at maximal intensity according to the prescribed work:rest ratio.

**Table 2 T2:** Progressively increasing training intensity in anaerobic exercises

Week	Goal	Sets^1^	Exercise duration	Intensity	Rest	Work:rest ratio
**1**	Familiarization with the exercises	5	15 s	95-100% HRmax	75 s	1:5

**2-3**	Built up training volume by decreasing work:rest ratio	5	15 s	95-100% HRmax	60 s	1:4

**4-6**	Built up training volume by increasing exercise duration	5	20 s	95-100% HRmax	80 s	1:4

**7-8**	Built up training volume by decreasing work:rest ratio.	5	20 s	95-100% HRmax	60 s	1:3

**9-16**	Maintain anaerobic capacity	5	20 s	95-100% HRmax	60 s	1:3

Abbreviation: HRmax = maximum heart rate

^1 ^In the anaerobic exercises, a set is a 15-20 seconds exercise. Children repeat each exercise 5 times, with a varying period of rest.

To collect information about the intensity of each training session, one child per training session will wear a heart-rate monitor that can store data and collects mean heart-rate data over 5-second intervals. The physiotherapists will fill in diary logs for each child to monitor their compliance with the training and the actual content of the fitness training. They will also register any adverse effects of the training, such as muscle soreness and other complaints about musculoskeletal pain. The range of motion and spasticity of the adductors, hamstrings, soleus and gastrocnemius muscles will be measured with the Spasticity Test (SPAT)[34] to evaluate any adverse effects of the training.

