## Background

Regular participation in physical activities is important for all children to stay fit and healthy. This is especially important for children with disabilities, who are often restricted in their activity options due to mobility problems. Cerebral palsy (CP) is the most common cause of physical disability in pediatric rehabilitation medicine and describes a group of disorders of the development of movement and posture, causing activity limitation, that are attributed to non-progressive disturbances that occurred in the developing fetal or infant brain[1]. Despite the non-progressive character of CP some children deteriorate in mobility related activities during childhood[2]. Current insights suggest that interventions for school-age children with CP should focus more on promoting an active lifestyle and increasing physical fitness[3]. This is the starting point of the LEARN 2 MOVE 7-12 study, that will evaluate a physical activity stimulation program in children with spastic CP aged 7 to 12 years. The LEARN 2 MOVE 7-12 study is part of the Dutch national LEARN 2 MOVE research program[4-6].

Children with CP have reduced levels of physical activity[7] and fitness[8-10] compared to typically developing children. A decrease in the level of fitness may reduce physical activity in a child with CP, and vice versa, which may result in a downward spiral of loss of muscle strength, reduced fitness and mobility, and in the long term, secondary complications due to inactivity, such as fatigue, pain, overweight, and osteoporosis[11]. This downward spiral should be broken in order to maintain current and future physical activity. This is especially important for young children, since achieving an active lifestyle between 9 and 18 years of age improves their prospects for an active lifestyle during adulthood[12].

Recent studies have shown that fitness training can improve physical fitness in children with CP[13,14]. In the only study[15] in which the effect of fitness training on both fitness and physical activity was investigated, no effect was found on physical activity[15], despite increases in fitness. The lack of a lifestyle intervention might explain this lack of effect, because positive effects on physical activity have been reported in children with no disabilities who participated in physical activity interventions[16], as well as in adults with disabilities who received counseling to adopt an active lifestyle[17].

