### Procedure

Children in the control group will continue with their regular pediatric physiotherapy. Since the content and frequency of the regular pediatric physiotherapy may differ among children, the physiotherapists will keep diaries about the treatment goals, and the intensity and frequency of physiotherapy sessions. Additionally, the content of the regular pediatric physiotherapy will be objectively determined by means of video-taping at least one physiotherapy session of each child. The children in the intervention group will participate in a 6-month physical activity stimulation program, instead of their regular pediatric physiotherapy. This program consists of: 1) a lifestyle intervention, combined with, 2) a fitness training program (see Figure 1).

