*CP-related quality of life *will be assessed with the CP-Quality of Life questionnaire[48] as a proxy parent-report. Five domains will be measured (social well-being and acceptance, functioning, participation, emotional well-being, pain and impact of disability) resulting in a total of 53 questions. The questions start with: 'How do you think your child feels about...?', and are scored on a 9-point scale.

*Self-reported fatigue *will be assessed with the PedsQL Multidimensional Fatigue Scale[49,50]. Three domains will be assessed (general fatigue, sleep/rest fatigue, and cognitive fatigue), and each domain contains six questions that start with: 'In the past month, how much of a problem has this been for you?'. The questionnaire (5-point scale) will be completed by the child, with help from the parents if necessary.

*Self-perception * will be assessed with Harter's Self Perception Profile for Children[51], adapted for children with CP[52]. The children will be assessed on three domains (motor competence, athletic competence, and global self-worth). Each domain has eight items, consisting of two opposite statements, such as "Some children think they are strong" and "Other children think they are not so strong". The children will be asked in an interview to choose which child they resemble most, and to indicate whether they are somewhat similar or very similar.

*Attitude towards physical activity *will be assessed in both the children and the parents by means of self-report. The children will have to indicate to what extent they agree with each of 14 statements, previously used in an intervention to improve physical activity in typically developing children[53]. The statements reflect eight advantages and six disadvantages of sport, for example "If I do sports, I have fun". Each statement is scored on a 5-point scale. The parents will have to indicate their opinion with regard to sports, and to what extent they agree with each of seven statements related to the accessibility of sports clubs, for example "I think my child is not good enough to join a sports club". Each statement is scored on a 5-point scale.

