### Statistical analysis

A sample-size calculation revealed that at least 22 children in each group are required to detect a difference in improvement of 1,000 steps per day between the intervention and the control group on the primary outcome. The power was 0.8, and the alpha was set at 0.05. This increase in steps per day seems to be clinically relevant, since improved health outcomes have been reported in adults after an increase of 1,000 in the amount of steps per day[54]. Taking into account drop-outs, 25 children will be included in each group.

Student *t*-tests will be performed to evaluate group differences at baseline, and a random coefficient analysis[55] will be performed to determine differences in change over time (treatment effect) between the control group and the intervention group. This method takes the dependency of children within physiotherapy practices and schools into account. An intention-to-treat analysis will be performed. The primary outcome (physical activity) and secondary outcomes (fitness, capacity of mobility, social participation, and health-related quality of life) will be the dependent variables in the analysis, with group allocation (control group or intervention group) and measurement occasion (time) as independent variables. The intervention effect will be evaluated by the group * time interaction. The alpha is set at 0.05. The influence of age, gender, and disease and environmental characteristics on the treatment effect will be investigated, and, if necessary, included as covariates in the analysis. The data will be analyzed with the Statistical Package for the Social Science, version 15.0 (SPSS Inc, Chicago, Illinois, USA).

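### Muscle soreness and musculoskeletal pain are registered only as effects of the training, in the trained arm, so these complaints have no control rate

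*Protocol article*

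**What the plan says.** The section on the fitness training program describes how the training is monitored: "The physiotherapists will fill in diary logs for each child to monitor their compliance with the training and the actual content of the fitness training". The next sentence, about the same physiotherapists, reads "They will also register any adverse effects of the training, such as muscle soreness and other complaints about musculoskeletal pain". The section then adds a second harm measure: range of motion and spasticity of named leg muscles "will be measured with the Spasticity Test (SPAT)[34] to evaluate any adverse effects of the training". It does not say in which arm or at which visits.

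For the comparator, the Procedure section says "Children in the control group will continue with their regular pediatric physiotherapy". Because that care varies, "the physiotherapists will keep diaries about the treatment goals, and the intensity and frequency of physiotherapy sessions". Complaints and adverse effects are not on this list.

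One further source bears on pain. Under Outcome measures, the CP-Quality of Life questionnaire is completed by the parent: "Five domains will be measured (social well-being and acceptance, functioning, participation, emotional well-being, pain and impact of disability". The article counts it under health-related quality of life, and the Statistical analysis section says that "secondary outcomes (fitness, capacity of mobility, social participation, and health-related quality of life) will be the dependent variables in the analysis, with group allocation" and time as independent variables.

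**The concern.** Soreness and musculoskeletal pain are the complaints that the article itself gives as examples of training harm. The collection rule has three features that together prevent a comparison.

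- **Definition.** The event is an effect of the training. A control child is not trained, so by definition cannot have one.
- **Recorder.** The entry is made by the person delivering the training, who knows the allocation and must decide whether the complaint was caused by it. The blinding in the Design section covers the assessors, not the trainers.
- **Comparator.** A diary exists for control children, but its described content leaves complaints out.

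The primary outcome is not affected. What is at stake is any statement about whether trained children had more soreness or pain complaints than children on regular physiotherapy. Complaints not written down in the control arm at the time cannot be reliably recovered later.

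**Working it through.** The article states no harm figure, so there is none to reproduce. The check sets the sections side by side and then shows what a one-arm count can and cannot say.

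**Step 1. Sources of harm data as described**

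| Source | Arm | Recorded by | Counts soreness or pain complaints? |
|---|---|---|---|
| Training logs (Fitness training program) | Intervention | Training physiotherapist, not blinded | Yes, if judged an effect of the training |
| Diaries of regular physiotherapy (Procedure) | Control | Treating physiotherapist | Not listed |
| SPAT (Fitness training program) | Not stated | Not stated | No: range of motion and spasticity |
| CP-Quality of Life pain domain (Outcome measures) | Both | Parent | No: a domain score that also covers impact of disability |

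Only the first row yields a count of complaints, and it has no counterpart in the control arm.

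**Step 2. What the one-arm count gives**

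Input: 25 children per group (Statistical analysis). The numbers with complaints are assumptions. The exact (Clopper-Pearson) 95% interval for x of n runs from the 2.5% point of Beta(x, n − x + 1) to the 97.5% point of Beta(x + 1, n − x).

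- 5/25 = 20%: 6.8% to 40.7%
- 10/25 = 40%: 21.1% to 61.3%

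These intervals describe the trained children only. They contain nothing about the excess over regular physiotherapy.

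**Step 3. What a control rate would add**

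Hold the trained arm at p1 = 0.40 and let the control rate p0 vary (assumed). The excess is d = p1 − p0, with Wald interval d ± 1.96 × √[p1(1 − p1)/25 + p0(1 − p0)/25].

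Worked case, p0 = 0.20: √(0.24/25 + 0.16/25) = √0.016 = 0.126; 1.96 × 0.126 = 0.25; d = 0.20, interval −0.05 to 0.45.

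| Control rate | Excess (points) | 95% CI (points) |
|---|---|---|
| 5% | 35 | 14 to 56 |
| 10% | 30 | 7 to 53 |
| 20% | 20 | −5 to 45 |
| 30% | 10 | −16 to 36 |
| 40% | 0 | −27 to 27 |

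The same 10 of 25 is compatible with every row. Registration in one arm cannot tell the first row from the last. The Wald interval is rough at the lowest control rate, where only 0.05 × 25 = 1.25 events are expected; the table is an illustration.

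**The case against.** Four arguments count against a stronger form of this point.

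**Harms in general are not without a comparison.** A reader might infer that the trial has no comparative harm data at all, or can say nothing about safety. The text does not support that. The pain domain is parent-reported, so it does not depend on the trainers, and it is analysed by group and time. SPAT is not restricted to one arm. This stands, and it limits the point to registered complaints of soreness and musculoskeletal pain. It does not remove the point, because neither measure counts such complaints.

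**The Background section does not establish background pain during the trial.** It mentions "secondary complications due to inactivity, such as fatigue, pain, overweight, and osteoporosis", but as long-term results of a downward spiral. It does not say that children of 7 to 12 will have such complaints during a four-month program, so the point cannot rest on it. Nor can one claim a given number of false entries. A background rate of 20% to 50% would give 25 × 0.20 = 5 to 25 × 0.50 = 12.5 children, but the rate is assumed, and the figure is an upper bound that requires every background complaint to be logged as a training effect.

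**The article never says that control complaints go unrecorded.** That is inferred from the diary content listed, and the full protocol may provide for general adverse-event reporting in both arms. This is fair, and a mere omission would not be worth raising. But the article goes further and describes a specific rule that differs between the arms. The point concerns that rule.

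**The gain is limited.** Safety relative to regular physiotherapy is not a stated aim, and two arms of 25 give wide intervals. This also stands. A wide interval around the right contrast can still be interpreted as a comparison; a one-arm count cannot.

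**Conclusion.** The point holds for registered complaints of muscle soreness and musculoskeletal pain. As described, they are collected only in the trained arm, only as effects of the training, and by unblinded trainers. They have no control rate.

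No figure in the article changes. The illustrated size is an excess anywhere from 0 to 35 points for the same 10 of 25 trained children. It rests on an assumed 40% in the trained arm and assumed control rates of 5% to 40%. The conclusion also assumes that no cause-neutral reporting in both arms is laid down in a document not shown.

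This is a cheap improvement to harm recording. It does not affect the primary comparison, and it does not show that the training is unsafe or that harms are otherwise unmeasured.

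**What to change.** 1. Add the same items to the diaries of the control-group physiotherapists and to the training logs: muscle soreness, musculoskeletal pain and other complaints, whatever the presumed cause. Record them over the same months in both arms.
2. Keep the judgement that a complaint was related to the training as an extra column, not as the condition for recording it.
3. Report the number of children with complaints by arm, and complaints per session, since session frequency may differ between arms.
4. State that SPAT is done in both arms at the same time points.

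The cost is a few lines on existing forms, slightly more diary work and one table by arm. Treatment, sample size and the primary analysis stay as they are. Two weaknesses remain. Ascertainment will still be unequal where children are seen at different frequencies, which the per-session figure only partly addresses. And the comparison will be imprecise: with 40% against 20% and 25 per arm, the interval still runs from −5 to 45 points. The items need to be in the diaries before recording starts.
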